**Sample size/power calculation**

The main analysis is on opiate substation treatment (OST) in primary care and risk of death and in particular the comparison of methadone and buprenorphine*.

There will be at least 20,000 OST patients (extracted from CPRD GOLD patients) from 1998 to 2014 linked to NHS central registry and ONS mortality data, that will generate 67,000 person years (pys) follow-up (~32,000 on treatment and ~35,000 off) if censored 12 months after last OST. There will be over 700 deaths of which ~500 will be due to overdose. This will be the largest study in the UK with precise data on OST treatment exposure (including ~ 12000 pys on buprenorphine and 30,000pys on methadone). In addition, there will be approximately 10,000 and 12,000 person years in treatments lasting less than 1 month or greater than 12 months, and 3000 and 1200 person years follow-up in the first 4 weeks treatment on or immediately after methadone or buprenorphine treatment respectively.

Thus, there is sufficient power (> 90%) to determine whether:-

1. there is at least a halving of the risk of death during treatment on burpenorphine compared to methadone (i.e. 0.35% vs. 0.69% respectively) – which requires a sample of at least 922 in each group compared to 12,000 and 20,000 on buprenorophine and methadone
2. and sufficient power (80%) to test if the risk of death is at least a 1/3 lower on buprenorphine at (0.006%) compared to methadone (0.016%) in the first 4 weeks of treatment (1200 and 3000 person years respectively) – as indicated by unpublished analyses by Degenhardt on Australian mortality cohort(9).

In addition, there is sufficient power to corroborate that the risk of fatal overdose out of treatment at 0.8% is twice as high as the risk during treatment – which will require sample of at least 788 in and out of treatment compared to our sample of over 30,000 person years in each group; and that the risk of death in the 4 weeks after treatment at about 4.6% is 1/3 lower (3.0%) for people treated for short duration of treatment (< 1 month) compared to those treated for 12 months or longer – which will require sample of at least 3123 in each group compared to over 3500 and 3850 person years among those exposed to short or prolonged treatment respectively;

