*Main outcome:* All and cause specific death (in particular drug poisoning/overdose) during drug treatment or follow-up period up to one year after date of last opiate substitution treatment (OST) prescription/treatment admission. Standard codes for drug related poisonings deaths will be used to define overdose deaths (23): ICD-10 codes: F11-16; F18-19; X40-44; X60-64; X85; Y10-14; as well as in terms of general and specific drugs mentioned on the death certificate (any opiate, heroin and Morphine, Methadone, buprenorphine, dihydrocodeine, other opiods, cocaine, all amphetamines and MDMA, GHB, GBL, all benzodiazepines, barbiturates, all antidepressants, paracetamol and other over the counter medicines). We will categorise deaths as “avoidable” and “preventable” based on ONS definitions (<http://www.ons.gov.uk/ons/publications/re-reference-tables.html?edition=tcm%3A77-262418>). Other specific causes that will be investigated include suicide and other injury (non drug related poisoning), infectious diseases, cirrhosis and liver disease. All cause mortality will be expressed as a rate and as a Standardised Mortality Ratio (SMR) compared to standard age and sex death rates for England and Wales. Cause specific mortality will be expressed as rates – and SMRs also will be calculated for non-drug related poisonings. Follow-up of patients extracted from primary care database (Clinical Practice Research Datalink, CRPD) will be from date of first OST prescription within risk period beginning 1990 to end 2011. A patient’s follow up will cease either one year after the expiry of their last prescription for OST or the date of death or on the date of transfer out from the general practice or risk study period end (which ever date occurs first). [Follow-up of patients extracted from Drug Data Warehouse (DDW) will be from 2005 to 2009 the period for which National Drug Treatment records are linked to the mortality register.] We are censoring follow-up twelve months after last prescription or specialist drug treatment date in order to reduce potential bias.

Secondary outcomes concern the practice and delivery of OST including:- annual number of people in OST; modality/specific OST drug; duration of OST; dose; evidence of reaching optimal dosage, tapering OST dose towards planned discharge, and supervised consumption; and co-prescription of benzodiazepines.

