Second, we will undertake analyses of patient characteristics in order to develop and use propensity scores that can be used to balance buprenorphine and methadone exposure groups and test for differences in mortality risk between the groups(25-27). The primary care databases hold a substantial amount of information on the patients’ diagnoses and treatment history as well as information on the practices – too much data to fit as individual covariates. Therefore, we can use these data to generate propensity score matching in order to use the score to reduce selection bias and match the patients exposed either to buprenorphine or methadone or to short or long term treatment(27).

Third, the problem of confounding (known and unknown) also will be addressed using self-controlled case-series (SCCS) methodology in which patients act as their own controls(28), as has been used in other studies of primary care databases(29, 30). In this method the number of events are classified according to the length of the exposure (in period; in and out of treatment) and an estimate of the hazard or incidence rate ratio is derived by conditioning on the number of events over the exposure history(28). Since there is missing information on risk of death prior to exposure only cases that have been exposed are included in the analysis. In addition, time invariant confounders (such as sex, age, underlying health problems) are controlled for implicitly; and time variant confounders can be fitted within the model. [name] and [name] are extending the SCCS method to deal with finite outcomes such as drug related/overdose death, and exposures that may persist (such as opiate substitution treatment) and this study will be a case study on how SCCS can be used with such exposures and outcomes. SCCS has been used for censored events – such as death previously (31, 32) – but classifying the exposure will require methodological development.

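### The self-controlled case series treats age as a fixed confounder, but only age at entry is removed by self-matching; current age has to be modelled

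*Protocol*

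**What the plan says.** The SCCS is the third of four approaches to confounding in the Protocol's Data/Statistical Analysis Plan. The text says that "time invariant confounders (such as sex, age, underlying health problems) are controlled for implicitly", and adds in the same sentence that "time variant confounders can be fitted within the model". It does not say which confounders belong to the second group. Because nothing is known about risk before exposure, "only cases that have been exposed are included in the analysis".

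Under Exposures, outcomes and covariates, follow-up "will be from date of first OST prescription within risk period beginning 1990 to end 2011", and a patient's "follow up will cease either one year after the expiry of their last prescription for OST", or at death, transfer out or study end if earlier. (The calendar dates differ between sections of the Protocol; that is a separate matter and does not affect this point.)

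The covariate list and the Poisson paragraph both name age, Charlson comorbidity, treatment episode number and calendar year as confounders known to affect mortality, and the Poisson rate ratios are to be adjusted for them. The plan then compares estimates across the four methods to judge how much residual or time-varying confounding remains.

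**The concern.** An SCCS conditions on the person, so it cancels anything constant over that person's observation time. Sex qualifies, and so does age at entry. Current age does not, nor does calendar time. The Protocol places age on the wrong side of its own division between fixed and varying confounders.

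The design makes this matter. Everyone enters on treatment and there is no earlier unexposed time. Where there is a final off-treatment period, it lies after all of that person's on-treatment time. Age and exposure are therefore ordered together within the person, and an age trend left out of the model passes partly into the off/on ratio.

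What is at stake is chiefly the interpretation. The SCCS is the only one of the four methods aimed at unmeasured fixed confounding. If the Poisson analysis adjusts for age and the SCCS does not, part of any difference between them comes from that omission and could be read as evidence about confounding.

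**Working it through.** The Protocol gives no estimate or sample size for the SCCS, so there is no figure of its own to reproduce. The check asks what value the SCCS tends to in large samples when age is left out.

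**Inputs from the Protocol (Sample size/power calculation)**
- "There will be at least 20,000 OST patients", "that will generate 67,000 person years (pys) follow-up (~32,000 on treatment and ~35,000 off) if censored 12 months after last OST".
- On treatment: 32,000 / 20,000 = 1.60 years per patient. Off: 35,000 / 20,000 = 1.75 years. Total: 67,000 / 20,000 = 3.35 years.
- Off/on ratio for fatal overdose: 2.
- Off-time after the last prescription is capped at 1 year, so on average at least 1.75 − 1.00 = 0.75 years must lie between episodes. Repeat episodes are implied by the Protocol's own figures.

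**Assumptions**
- The log death rate changes by b per year of age. No gradient is given, so a range is used.
- The split of the 1.60 and 1.75 years into episodes is assumed.
- Each person's planned exposure windows are treated as known, which sets aside the separate problem that death ends observation.

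**Formula.** Let the true rate be proportional to 2^(off) × exp(bt), with t in years since entry. If everyone has the same pattern, the SCCS without age tends to

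2 × (mean of exp(bt) over off-time) / (mean of exp(bt) over on-time).

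*One episode, 1.6 years on then 1 year off:*
- b = 0.04: 2 × 1.0877 / 1.0327 = 2.11
- b = 0.08: 2 × 1.1833 / 1.0668 = 2.22

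*Two episodes, 0.8 on, 0.75 off, 0.8 on, 1 off (totals 1.60 and 1.75):*
- b = 0.04: 2 × 1.0897 / 1.0487 = 2.08
- b = 0.08: 2 × 1.1888 / 1.1009 = 2.16

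Real durations vary between people. With exponential durations at the same means (the final year off kept fixed), the score equation of the conditional likelihood is solved numerically:

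| Pattern | b = −0.03 | b = 0 | b = 0.04 | b = 0.08 |
|---|---|---|---|---|
| Two episodes, 1.60 on / 1.75 off | 1.93 | 2.00 | 2.10 | 2.20 |
| One episode, 1.60 on / 1.00 off | 1.90 | 2.00 | 2.15 | 2.31 |

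The two-episode row matches the planned person-years. The one-episode row does not, because it has only 1 year off per person. With age fitted and the model otherwise correct, the ratio is 2.00.

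**Long treatment.** For 10 years on and 1 year off with b = 0.05, the limit is 2.61. This is an extreme pattern, given a mean follow-up of 3.35 years.

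**Against random error.** In the two-episode set-up with the planned 700 deaths, the 95% interval for the log ratio is about ±0.17. The bias on that scale is ln 1.05 = 0.05 to ln 1.10 = 0.10. If only 30% of 700 deaths were overdoses (210, taking the share reported in the December 2015 amendment), the interval is about ±0.31.

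**The case against.** The strongest reply is that the Protocol never says age will be omitted. The same sentence allows time-varying confounders to be fitted, age is listed as a confounder elsewhere, and the SCCS is openly described as needing methodological development. That stands as far as it goes: a reader might infer that age is to be left out, and the text does not settle it. But the text does say that age is already dealt with. Someone following it would have no reason to fit age. That is a wrong statement, not a detail left for later.

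Four stronger readings are tempting and are not supported.
- *That the bias must exaggerate the benefit of treatment.* This holds only if the risk rises with age. The emphasised outcome is overdose death, no gradient is given, and a falling risk reverses the sign.
- *That a calendar window of well over a decade makes the bias large.* Mean follow-up is 3.35 years, and off-time between episodes weakens the link between age and exposure.
- *That the key comparison of buprenorphine with methadone is biased.* Nothing here shows that; the check concerns off versus on only.
- *That health problems must be struck from the list altogether.* Underlying conditions can mean those present at entry, which self-matching does remove. Time-updated comorbidity may itself be affected by earlier treatment, which is the Protocol's own reason for its fourth method, so it should not be a mandatory term.

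It is also fair that the shift is smaller than the random error and would not overturn a two-fold ratio.

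**Conclusion.** The point holds in a limited form. Classing age as fixed is an error of principle, and the design turns it into a bias in the off/on ratio if age is left out. Under the assumed slopes of 0.04 to 0.08 per year, the bias is about 5 to 10% upward with repeat episodes that fit the planned person-years, and up to about 16% (2.31 against 2.00) with a single episode. At a slope of −0.03 it becomes 3 to 5% downward (1.93 and 1.90). These figures rest on assumed gradients and an assumed split of episodes. The main consequence is a less trustworthy comparison between the SCCS and the age-adjusted Poisson analysis.

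**What to change.** In the SCCS paragraph:
- Replace age with age at entry in the list of implicitly controlled confounders.
- Limit underlying health problems to conditions fixed at entry.
- State that current age, in bands, and calendar period enter the SCCS as within-person time-varying terms.
- Use time-updated comorbidity only in a sensitivity analysis.

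This costs about a sentence of text and a few model parameters. The downside is a small loss of precision.

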**Use of linked data**

We will use link to ONS mortality file for our outcome measures. **Data/ Statistical Analysis Plan**

1) We expect that overdose and drug related mortality risk differs by period of treatment exposure (1-4 weeks treatment start, rest of treatment duration, 1-4 weeks treatment end, 5-52 weeks out of treatment). The main analysis will test whether there is evidence of a difference in mortality risk by modality of OST (methadone vs. buprenorphine) at different periods on and off treatment – and will investigate also mortality risk in relation to additional exposures (co-prescription of benzodiazepines, measures of treatment performance/quality) and confounders (age, gender, co-morbidity as defined by Charlson Index(24), alcohol and mental health problems, treatment episode number, calendar year) all of which have been shown to influence mortality risk(11) (9). However, other potential confounders or factors relating to injecting risk may be missing or incompletely measured in CRPD (such as crack-cocaine use).

We will undertake a series of analyses that aim to incorporate and adjust for confounding.

First, we will use Poisson regression incorporating time varying covariates (such as co-prescription of benzodiazepines, episode and duration of treatment) to describe mortality risks and compare these at different periods on and off treatment and by modality of OST. These analyses will generate incidence rate ratios (IRR) that compare mortality risk for patients on methadone (from week 4 to end of treatment as baseline) to other periods and other forms of OST; will compare mortality rate for key confounders (above); adjust IRR by period on or off treatment for these confounders; and examine specifically whether co-prescription of benzodiazpeines increases the risk of mortality during and after treatment.

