Fourth, even in the absence of unmeasured confounding, conventional methods (eg regression models that control for baseline or time-dependent confounders) will provide estimates that may fail to have a causal interpretation when (i) there is a measured time-dependent risk factor for survival that also predicts subsequent treatment, and (ii) past treatment history predicts the subsequent level of this risk factor. We will use inverse probability (IP) weighted estimation of marginal structural models, which avoids conditioning on time-dependent confounders(33, 34). Instead, we estimate the inverse of each patient’s probability of their observed treatment history at each time. By weighting a marginal model according to the reciprocal of these probabilities, we mimic a situation in which the assignment to treatment is at random (or unrelated to the time-varying covariates).

By examining the intervention effects between exposure and outcome and how they vary across multiple methods which adjust for confounding in different ways we will be able to assess the likelihood that residual/time-varying confounding remains a significant problem, and to contribute stronger evidence on the impact of treatment on drug related mortality(35, 36). Similar analyses will be conducted on the risk of mortality during and after exposure to non-pharmacological treatments(18).

2) The secondary analysis of clinical databases will test whether there have been changes over time in the number of patients treated over time and specifically in the delivery of OST in primary care (e.g. the mean dose, treatment duration, modality and evidence of supervised consumption). Segmented regression techniques will be used for time trend analyses of these treatment indicators in order to test whether there have been changes over time, and whether the timing of the change is consistent with issuing of new treatment guidelines(20, 37).

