**Limitations of the study design, data sources and analytic methods**

The key limitation is confounding – which we discuss and seek to address in our analysis plan above. Multiple analyses will be undertaken running the risk of “statistical multiplicity” and we will guard against over-interpretation of single statistical tests(42). The key hypothesis to be tested is whether there is evidence that buprenorphine is a safer substitution drug (in relation to mortality risk) than methadone. In addition, we will corroborate earlier analyses that hypothesised that mortality risk was elevated compared to other periods immediately after treatment cessation. Several analytic approaches will be presented in order to consider the extent of confounding and to aid interpretation of the analyses.

There are missing prescription data which may lead to misclassification of periods on and off (e.g. missing amount prescribed or daily dose in order to determine last date of prescription) – which we will subject to sensitivity analysis – including using different definitions/criteria for when a patient is on/off OST and using only the last prescription. Some patients maybe treated in specialist drug treatment clinics as well as primary care, which may introduce a potential bias if the information on other periods on OST is unrecorded. We will undertake analyses to estimate the frequency of this occurrence and how CPRD can be used to identify these periods. Periods in prison are unlikely to be recorded which also may introduce bias and confer additional risks (e.g. the period in prison will be at lower mortality risk but the period immediately following prison release is a period of high risk(43)). We can estimate the likely frequency and proportion of these events from other analyses to assess potential bias, and take these biases into account in the interpretation of our findings.

The analysis of CPRD will describe mortality risk for different periods on and off treatment for further mathematical models – which include other information – such as proportion of opiate dependent people in treatment. These also are subject to uncertainty and will be explored in sensitivity analyses.

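### Comparing the four planned methods cannot rule out unmeasured time-varying confounding, yet the protocol says the comparison will show how likely residual confounding is

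*Protocol*

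**What the plan says.** Item 1 of the protocol's Data/ Statistical Analysis Plan lists four analyses.

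- **Poisson regression** with time-varying covariates, which will "adjust IRR by period on or off treatment for these confounders" (age, gender, Charlson index, alcohol and mental health problems, episode number, calendar year).
- **Propensity scores**, built from a wider recorded set of diagnoses, treatment history and practice data, described as "too much data to fit as individual covariates".
- **SCCS**, in which "time invariant confounders (such as sex, age, underlying health problems) are controlled for implicitly" and time-varying confounders can be fitted. For this exposure the protocol adds that "classifying the exposure will require methodological development".
- **Weighted MSM**, introduced for measured time-dependent confounders that are affected by past treatment.

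The section then draws a conclusion from comparing the estimates of these four analyses, on the premise that each handles confounding differently: "we will be able to assess the likelihood that residual/time-varying confounding remains a significant problem". The same item concedes that "factors relating to injecting risk may be missing or incompletely measured in CRPD (such as crack-cocaine use". The Limitations section repeats the idea: "Several analytic approaches will be presented in order to consider the extent of confounding". It also names the relative safety of buprenorphine and methadone as the key hypothesis.

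**The concern.** Variation between methods reveals a confounder only if at least one method handles that confounder and another does not. Three of the four methods assume no unmeasured confounding. If an unrecorded factor drives both the choice of drug and death, those three estimates carry broadly the same bias. The fourth removes fixed factors, but not unrecorded factors that change over time, and changing drug use is such a factor. The quoted sentence covers time-varying confounding without distinguishing measured from unmeasured.

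Similar estimates could therefore be taken as reassurance on the key buprenorphine hypothesis when the comparison could not have exposed the bias. The effect estimates also feed the population model of drug-related deaths (item 3 of the same plan) and are meant to inform treatment guidelines (Objective section).

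**Working it through.** The protocol gives no figure on this point, so there is none to reproduce. The inputs below are assumptions unless marked as the protocol's.

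**1. What each contrast can show**

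| Contrast | Confounding it can reveal |
|---|---|
| Poisson vs propensity score | recorded variables not on the Poisson list |
| Poisson vs MSM | measured time-dependent confounders affected by past treatment |
| SCCS vs the other three | unmeasured time-fixed factors, subject to precision |
| none | unmeasured time-varying factors |

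**2. Simulation of that table**

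Setting: 40,000 patients, 6 intervals, true rate ratio 0.50, about 2,000 to 2,500 deaths, 6 replicates. Unmeasured factors had coefficient 0.8 on the log odds of treatment and 0.7 on the log death rate. SCCS was idealised: the planned exposure history was taken as known even after death.

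| Confounding | Poisson | Propensity | MSM | SCCS |
|---|---|---|---|---|
| No unmeasured | 0.50 | 0.50 | 0.51 | 0.50 |
| Unmeasured, fixed | 0.76 | 0.77 | 0.76 | 0.49 |
| Unmeasured, time-varying | 0.82 | 0.83 | 0.83 | 0.83 |

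In a fourth case, a measured confounder was affected by past treatment. The true lagged-treatment ratio is exp(0.7 × −0.8) = exp(−0.56) = 0.57. Poisson gave 1.02 and MSM 0.59.

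So the comparison works in the second and fourth cases and fails in the third. Two features favour agreement: all three recorded-covariate methods used the same covariates, and the time-varying factor was drawn afresh in each interval. SCCS would remove part of a slowly changing factor.

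**3. Size of a possible bias in the drug comparison**

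For an unmeasured binary factor with prevalence p_B on buprenorphine and p_M on methadone and death ratio R, and no drug effect, the apparent ratio is

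[1 + p_B(R − 1)] / [1 + p_M(R − 1)].

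- With p_B = 0.20, p_M = 0.40, R = 3: 1.4/1.8 = 0.78.
- With the prevalences exchanged: 1.8/1.4 = 1.29.
- At 20% versus 40%, the ratio runs from 1 (R = 1) towards 0.20/0.40 = 0.50 as R grows.

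The protocol's power target is 0.35% against 0.69%, a ratio of 0.51. Dividing by 0.78 leaves 0.65, so a confounder of this strength would not by itself explain a halving.

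**4. Could SCCS expose a false 0.78?**

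Take the most favourable case: the factor is fixed and SCCS centres on 1. Assume 20 to 100 deaths in patients exposed to both drugs, SE = 2/√deaths (0.447 to 0.200), and a Poisson SE of 0.085. The distance is |ln 0.78| = 0.248.

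- 20 deaths: combined SE √(0.200 + 0.0072) = 0.455, z = 0.55, chance of a significant difference 8%.
- 100 deaths: √(0.040 + 0.0072) = 0.217, z = 1.14, chance 21%.

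A Poisson SE of 0.12 gives 8% to 19%. If the shared cases make the variance of the difference SE²(SCCS) − SE²(Poisson), SE 0.12 gives 9% (20 deaths) to 34% (100 deaths; √(0.040 − 0.0144) = 0.160, z = 1.55).

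The sample size section expects over 700 deaths in all, about 500 of them from overdose. The December 2015 amendment reports fewer deaths than expected, with 30% identified as overdose or drug related, and hopes that new linkage will help.

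**The case against.** A reader might infer that the comparison cannot discriminate at all, or that agreement is almost guaranteed whether or not confounding is present. The protocol does not support that.

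- SCCS is included to deal with unknown as well as known confounding, and in idealised form it departs clearly under an unmeasured fixed factor (0.49 against 0.76).
- Poisson against MSM detects the problem for which the MSM was introduced.
- The propensity score draws on more recorded data than the Poisson model, so the three methods do not use identical covariates and need not coincide.
- No agreement criterion is written down. The Limitations section treats the several approaches as an aid to interpretation, calls confounding the key limitation and warns against over-reading single tests.
- The imprecision of SCCS concerns a direct drug-against-drug contrast. For on- against off-treatment contrasts, patients who used one drug also contribute. An indirect drug comparison through off-treatment time would use more deaths, though it then compares effects estimated in different people.
- A non-significant difference between SCCS and Poisson is not the same as agreement.

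All of this stands and limits the point. It does not rescue the quoted sentence for unmeasured time-varying factors, which no contrast addresses. The Limitations section plans some assessment of unrecorded prison periods and specialist-clinic treatment, but states none for crack-cocaine use. Detail of a bias analysis could sit in a statistical analysis plan that is not shown. The sentence that overstates what the comparison achieves is in the protocol.

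**Conclusion.** The point holds in a limited form. Agreement of the Poisson, propensity and weighted estimates speaks only to how measured confounders are chosen and modelled. SCCS adds a check on unmeasured fixed factors. For methadone against buprenorphine that check may be imprecise, and the protocol says its exposure classification still has to be developed. Under unmeasured time-varying confounding all four methods can agree and be wrong, as in the simulated 0.82 to 0.83 against a truth of 0.50.

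The logic rests on the protocol's description of the methods; the sizes rest on assumptions. One illustrative simulation had 20,000 patients, about 296 on-treatment deaths, no drug effect and the 40%/20%/ratio 3 confounder. All three recorded-covariate methods gave 0.79, and Poisson was significant in 48% of runs. With the 8% to 21% above, it is tempting to say that the methods would appear to agree in about 80% to 90% of studies with a false reduction. That depends on one assumed confounder, an assumed number of deaths in patients exposed to both drugs, and counting non-significance as agreement. These figures are not properties of this study. The change should be made, but the flaw does not invalidate the four analyses.

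**What to change.** In item 1 of the Data/ Statistical Analysis Plan, replace the general claim with a statement of which contrast addresses which type of confounding, as in the first table under the working. Say plainly that none addresses unmeasured time-varying factors, and carry the same wording into Limitations.

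Add one of two analyses for the methadone-buprenorphine rate ratio:

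- a quantitative bias analysis over stated ranges of confounder prevalence by drug and effect on death, with crack-cocaine use as the named example; or
- the confounder strength needed to move the ratio, and its confidence limit, to 1.

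Interpret any claim that buprenorphine is safer in light of that result. The cost is wording and a short analysis on the same data, with no new extraction. The downside is that the conclusion may have to be more cautious. If the observed effect is large, the same analysis could strengthen it.
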